### Sample size

We will consider a difference of 0.5 standard deviation, which is equal to a moderate effect size [29], clinically relevant. For calculating the required difference on the Inflammatory Bowel Disease Questionnaire (IBDQ), we will use the data from a study by McColl et al [30] among 111 IBD patients. The mean IBDQ score was 182 and the standard deviation was 59. A 0.5 standard deviation thus equals approximately 30 points on a scale ranging from 32 to 224. With an effect size of 0.5 standard deviation, an alpha level of 0.05, and a power of 80%, at least 34 patients in both the experimental condition and the waiting list control condition are needed. Given a potential attrition rate of 10%, we will include 40 patients in each condition.

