### Statistical analysis

Analyses of covariance will be conducted to determine the extent to which treated patients (experimental condition) show more improvement on the primary and secondary outcome variables compared to patients in the waiting-list control condition. A two-way factorial analysis of variance with the between-factor condition (experimental condition versus waiting list control condition) and the within-factor assessments will be used. Moreover, stratification variables, i.e. gender, treatment center and disease type will be included as covariates in the analyses (ANCOVA).

Additionally, the data of experimental and the waiting-list control condition will be pooled, to measure the overall effect of treatment. Before the two groups will be pooled, we will examine whether there is a difference in effect for the experimental versus the waiting-list control condition (Delta T_follow-up after CBT_-T_baseline before CBT_). In case differences emerge, this will be stratified reported.

For therapy effects, data will be analysed on an intention to treat (ITT) as well as treatment completer basis. The completers sample will include patients who attend at least 5 CBT sessions.

To express the magnitude of the effects, mean gain scores on the outcome measures will be standardized to Cohen’s *d*, representing the number of standard deviations separating the two means. Point estimates and 95% confidence intervals of *d* will be determined for the within and the between group effects. Between effect sizes will be calculated using the pooled standard deviation (of the baseline scores) and confidence intervals will be approximated from the central *t*-distribution.

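### The between-group analysis is described both as ANCOVA and as a condition-by-assessment ANOVA, and baseline IBDQ is not named as a covariate; one baseline-adjusted ANCOVA would be clearer and more powerful at no cost

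*Protocol article*

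**What the plan says.** All of this is in the protocol article.

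- **Statistical analysis, purpose.** "Analyses of covariance will be conducted to determine the extent to which treated patients (experimental condition) show more improvement" than waiting-list patients on the primary and secondary outcomes.
- **Statistical analysis, structure.** The next sentence specifies a two-way ANOVA with condition as the between-patient factor and assessment as the within-patient factor. It does not list the assessments that enter, or say whether the test of interest is the main effect or the interaction.
- **Statistical analysis, covariates.** "stratification variables, i.e. gender, treatment center and disease type will be included as covariates in the analyses (ANCOVA").
- **Statistical analysis, effect size.** "mean gain scores on the outcome measures will be standardized" to Cohen's d; the between-group d uses the pooled baseline SD.
- **Methods and design, and Table 1.** Both arms complete the IBDQ at baseline, and randomisation follows. The control arm has one further assessment, after waiting about 3.5 months, before its own CBT starts. That wait is set to match the treatment and follow-up of the experimental arm.
- **Sample size.** "We will consider a difference of 0.5 standard deviation, which is equal to a moderate effect size". The section sets alpha at 0.05 and power at 80%, and concludes that "at least 34 patients in both the experimental condition and the waiting list control condition are needed". To allow for 10% dropout, the target is 40 randomised per arm. The section mentions neither a baseline-to-follow-up correlation nor baseline adjustment.

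**The concern.** Two things are left badly fixed.

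First, the text gives two descriptions of the main comparison and calls neither primary. A reader cannot tell whether the treatment effect will be judged on follow-up scores adjusted for covariates, or on the interaction in a repeated-measures layout.

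Second, the strongest available covariate is probably the patient's own baseline IBDQ, and it is not among those named. If the repeated-measures layout is what will be run, baseline is used, but only by subtraction: the whole baseline difference is removed from the follow-up difference. With equal variances at the two times, ANCOVA removes only r times it. Subtraction therefore over-corrects a chance baseline imbalance and carries more noise.

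At stake is precision in a trial with about 36 evaluable patients per arm. The size of the treatment effect is not at stake: under randomisation both approaches estimate the same quantity.

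**Working it through.** **Inputs.** From the Sample size section: difference 0.5 SD, alpha 0.05, power 80%, 34 needed per arm, 40 randomised per arm, 10% attrition. Evaluable patients per arm: 40 × 0.9 = 36. Assumed, because the article does not say: a two-sided test; equal baseline and follow-up SDs; correlation r from 0.3 to 0.8.

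**The plan's own figure.** For a two-arm comparison of means at d = 0.5, two-sided 0.05 and 80% power, the t-test needs 63.8, so 64 per arm (63 by the normal approximation). The stated 34 does not reproduce. A paired or one-sample t-test at d = 0.5 gives 33.4, rounded up to 34, but that is not the between-arm test. Since 34/63 = 0.54, a two-arm 34 would require:

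- baseline-adjusted ANCOVA with 1 − r² = 0.54, so r about 0.68; or
- a change score with 2(1 − r) = 0.54, so r about 0.73.

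The article states neither. The sample size is a separate matter; it is relevant here because it leaves little power to spare.

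**Why the interaction is a change-score test.** During the randomised period the control arm has exactly two assessments. The experimental arm's mid-treatment assessment has no untreated counterpart, because the control arm's mid-treatment assessment falls during its own CBT. With two time points, the condition-by-assessment interaction is the difference between arms in mean change.

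**Variances** (per patient, in units of SD²):

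- change score: 2(1 − r)
- ANCOVA on baseline: 1 − r² = (1 − r)(1 + r)
- ratio: 2/(1 + r)

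**Power.** With variance v, the noncentrality is (0.5/√v) × √(36/2) = 2.121/√v, on 70 degrees of freedom (noncentral t). The few degrees of freedom spent on covariates are ignored.

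| r | Variance, change | Variance, ANCOVA | Ratio | Power, change | Power, ANCOVA |
|---|---|---|---|---|---|
| 0.3 | 1.40 | 0.91 | 1.54 | 42% | 59% |
| 0.5 | 1.00 | 0.75 | 1.33 | 55% | 68% |
| 0.7 | 0.60 | 0.51 | 1.18 | 77% | 83% |
| 0.8 | 0.40 | 0.36 | 1.11 | 91% | 94% |

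The normal approximation agrees to within about 1 point; at r = 0.8 it gives 92% against 94%. Comparing follow-up scores with no use of baseline has v = 1 and power of 55% at any r.

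**If the variances differ.** Let the follow-up SD be k times the baseline SD. The change-score variance is then 1 + k² − 2rk and the ANCOVA variance is k²(1 − r²). The first minus the second is (1 − rk)², which is never negative. So ANCOVA is at least as precise whatever k is, but the ratio moves. At r = 0.5 it is 1.75 for k = 0.8 and 1.12 for k = 1.25. At r = 0.8 and k = 1.25 it is exactly 1, with no gain.

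**The case against.** The strongest reply is that the three sentences describe one model: the first gives its purpose and class, the second its between/within structure, and the third adds covariates. That reading is possible, and the text labels neither description primary. A reader might infer two rival primary tests to be chosen between once the data are seen; the article does not support that charge, only that its wording fails to settle the model.

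A reader might also infer that baseline IBDQ is ignored. That is not supported either. Baseline is a level of the within-patient factor and is built into the gain scores. The opening reference to ANCOVA might even intend a baseline covariate, although the text does not say so. What can be said is that baseline is not named as a covariate.

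A third tempting reading is that Cohen's d will not match the primary test. If the test is the interaction, gain scores match it. A mismatch arises only if a baseline-adjusted ANCOVA is used and d is still taken from raw gains.

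Two further objections stand. A change-score analysis controls type I error and is unbiased under randomisation, so this is a matter of efficiency and does not correct an invalid test. And the gain depends on an r that the article does not give; at r = 0.8 it is 2 to 3 points.

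It might finally be said that covariate lists belong in an analysis plan. But the article goes beyond silence: it sets out a model structure, names covariates and defines the effect size. What it sets out can be improved with data the trial already collects.

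**Conclusion.** The point holds as a free improvement and a clarification. The article should settle on one analysis, and on the condition-by-assessment reading the analysis it describes is less efficient than ANCOVA on baseline. With equal variances, 36 per arm and a 0.5 SD effect, the cost is about 17 power points at r = 0.3, 12 to 13 at 0.5, 6 at 0.7 and 2 to 3 at 0.8. The direction does not depend on r or on equal variances; the size does. It cannot be fixed from the document, so this should not be presented as the largest gain available to the trial. Nor does baseline adjustment by itself rescue the sample size: it supports 34 per arm only if r is about 0.68 or higher.

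**What to change.** State one primary analysis: ANCOVA of IBDQ total at the end of the randomised period (about 3.5 months) on condition, with baseline IBDQ, gender, disease type and center type (academic or peripheral, as used in the stratification) as covariates. Analyse each secondary outcome the same way, with its own baseline. Do not use the condition-by-assessment ANOVA as the test of the treatment effect. Report the between-group d as the adjusted difference and its confidence interval divided by the baseline SD, so that it matches the test. State the r assumed in any power statement.

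The cost is a few sentences in the analysis section or analysis plan, settled before outcome data are examined. No extra data, visits or patients are needed.

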Participants assigned to the experimental condition will start treatment as soon as possible (maximum within 6 weeks). The second, mid-treatment assessment will take place four weeks following start of treatment and the third assessment one month following completion of treatment. Following the first baseline assessment, participants assigned to the waiting-list control condition will wait 3,5 months before they are treated with CBT. This period corresponds to the duration of the CBT intervention and follow-up assessment of the experimental group. After this 3,5 month waiting period the participants in the waiting-list control condition will be asked to complete a follow-up after waiting/baseline before CBT assessment before starting treatment. Analogous to the procedure in the experimental condition, the mid-treatment assessment will take place four weeks following start of treatment and the follow-up assessment one month following completion of treatment (see Table 1).

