#### Feasibility

Approximately 1600 IBD patients are treated at the AMC on a yearly basis. Given the fact that patients may be eligible regardless of time since diagnosis, the number of patients to be included in only one center is feasible. However, to enhance recruitment in a relatively short time period and promote future dissemination we will recruit patients in three additional medical centers (i.e. Slotervaart-hospital, Flevo-hospital and VUmc). Two of the four participating centers are academical medical centers (i.e. AMC and VUmc). Based on the literature [31], we expect 10-20% of the IBD patients to have a score below the cut-off point and be eligible for the study.

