### Recruitment and informed consent

Patients who have a score of 23 or lower on the mental health subscale will be eligible for the study. The mental health subscale consists of 5 items that require a response on a 6-point scale (range 5–30). The cut-off score of 23 is chosen as scores of 23 or lower are found indicative (with a high level of sensitivity and specificity) of depression and anxiety in primary care patients [17]. If this step is ignored a failure of a positive effect may be contributed to high baseline scores and lack of room for further improvement [15]. Consequently, the researcher will contact patients by telephone to ask whether they are willing to participate and to check whether informed consent is received. If the participant meets all inclusion criteria and is willing to provide informed consent, an appointment will be made to administer the SCID-I by telephone.

The SCID-I will be used as a screening measurement before randomisation.

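### The planned pooling of both arms' before-to-after CBT change is an uncontrolled pre-post comparison and cannot measure the effect of treatment; comparing the two arms' changes first does not cure this

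*Protocol article*

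**What the plan says.** The Statistical analysis section of the protocol article opens with an analysis of covariance comparing the experimental and waiting-list conditions. As an additional step it states that "the data of experimental and the waiting-list control condition will be pooled, to measure the overall effect of treatment". The quantity is the change from the baseline before CBT to the follow-up after CBT. The section adds: "Before the two groups will be pooled, we will examine whether there is a difference in effect", and then "In case differences emerge, this will be stratified reported". It gives no test, margin or criterion for that check. It also plans 95% confidence intervals of Cohen's d for within-group as well as between-group effects.

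Three other places bear on this:

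- **Methods and design, text after Table 1:** "participants assigned to the waiting-list control condition will wait 3,5 months before they are treated with CBT". Controls are reassessed after the wait and before their CBT. The experimental arm has one pre-treatment assessment and starts CBT within at most 6 weeks.
- **Recruitment and informed consent:** "Patients who have a score of 23 or lower on the mental health subscale will be eligible for the study".
- **Feasibility:** "we expect 10-20% of the IBD patients to have a score below the cut-off point".

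**The concern.** Once controls start CBT, no untreated group remains. The pooled change therefore contains the CBT effect plus whatever would have happened anyway: regression to the mean after selection on a low score, the fluctuating course of the disease (which the Background calls unpredictable), and other care. The waiting list exists to remove these components, and pooling the two treated phases discards that protection.

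The pooled figure also looks more precise than the controlled one. A non-significant randomised result could sit beside an apparently clear overall effect, under a label that tells the reader it measures treatment.

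The step before pooling offers little reassurance. It asks whether the two changes differ from each other, not whether either is free of drift. If they do differ, reporting by arm leaves each arm's change just as uncontrolled.

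**Working it through.** **Inputs from the document.** The IBDQ SD is 59 and the relevant difference 0.5 SD: 0.5 × 59 = 29.5 points, which reproduces the plan's figure of about 30. There are 40 patients per arm with 10% attrition: 40 × 0.9 = 36 per arm, 72 pooled. The selected fraction is the lowest 10-20%. The plan gives no figure of its own for the pooled analysis or for the check before it.

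**Assumptions, because the document gives no values.** The pre-post correlation ρ of the IBDQ is 0.5 to 0.8. The check is a two-sided t-test at 0.05. The correlation of the IBDQ with the screening score, and how fast it decays, are assumed in step 4.

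**1. What the pooled change contains.** Write each arm's expected change as τ + g, where τ is the CBT effect and g the untreated drift, with g_E for the experimental arm and g_C for controls. With equal numbers and the same τ:

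- pooled change = τ + (g_E + g_C)/2
- difference examined before pooling = g_E − g_C

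If g_E = g_C the difference is zero whatever the size of the drift, so the check is passed at any sample size and the bias stays in full.

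**2. The 'before' points differ.** If the 6 weeks are counted from baseline, the experimental arm's change spans up to 6 + 8 + about 4 = 18 weeks. For controls who start straight after reassessment it spans 8 + about 4 = 12 weeks, beginning 3.5 months after their first baseline. There is thus no reason to expect g_E = g_C.

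**3. Power of the check, if it is a test.** In baseline SD units the SD of change is s = √(2(1 − ρ)), the standard error is s√(2/36), and power comes from the noncentral t with 70 df.

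| ρ | s | SE | power, 0.25 SD | power, 0.5 SD |
|---|---|---|---|---|
| 0.5 | 1.000 | 0.236 | 18% | 55% |
| 0.7 | 0.775 | 0.183 | 27% | 77% |
| 0.8 | 0.632 | 0.149 | 38% | 91% |

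**4. Possible size of untreated drift.** Under normality the mean screening score of the lowest fraction p lies φ(z_p)/p SD below the clinic mean: 1.755 for p = 0.10 and 1.400 for p = 0.20. Drift on the IBDQ is this distance times the fall in its correlation with the screening score between the 'before' and 'after' points.

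- Low end: correlation 0.4, of which 10% is lost, so a fall of 0.04. 1.400 × 0.04 = 0.056 SD, or 0.056 × 59 = 3.3 points.
- High end: a fall of 0.20. 1.755 × 0.20 = 0.351 SD, or 0.351 × 59 = 20.7 points.

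These apply to a group assessed soon after screening. If drift in controls had died out by the end of the wait (assumption), the pooled drift would be half: 0.03 to 0.18 SD.

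**5. Consequence for the pooled figure.** On change scores the pooled standard error is s/√72 = 0.118s, against s√(2/36) = 0.236s for the randomised contrast, so it is half as large at any ρ. Suppose CBT has no effect, drift is 0.2 SD in both arms, and the pooled change is tested two-sided at 0.05 (normal approximation):

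- ρ = 0.5: 0.2/0.118 = 1.70, significant in about 40% of trials.
- ρ = 0.7: 0.2/(0.118 × 0.775) = 2.19, significant in about 59%.

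With drift of 0.2 SD in the experimental arm and 0.1 SD in controls, the pooled change is significant in about 25% (ρ = 0.5) to 38% (ρ = 0.7). The check detects that 0.1 SD difference in only about 6-8%.

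**The case against.** The strongest reply is that the pooled analysis is supplementary. The section begins with the randomised ANCOVA, and nothing lets the pooled figure replace it. This stands. A reader might infer that the trial's main conclusion is compromised, or that the plan would claim effectiveness from the pooled result after a null randomised one. The document sets no such rule and states no significance test of the pooled change. What remains is an analysis whose stated purpose it cannot serve.

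A second reply is that the plan only says it will examine a difference. A reader might infer a formal, low-powered significance test. The document names none, and a condensed article may leave such detail out. Power also depends on the correlation: at 0.5 SD, the plan's own relevant difference, it ranges from 55% to 91%. So low power is not established in general, though it is low for 0.25 SD throughout the assumed range. The objection to the check does not rest on power, since equal drift escapes it regardless.

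A third reply concerns the drift. Selection is on the SF-36 and the outcome is the IBDQ. Baseline follows screening, a telephone call about a week later, a consent meeting and the SCID-I, so some regression has already occurred. Controls start their change 3.5 months later still. This also stands: the upper drift values should not be read as the bias of the pooled estimate.

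Finally, the controls' change during the wait is already collected and within-group effects are already reported. This makes the remedy cheap, but the treatment-effect label remains.

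**Conclusion.** The concern holds as a point about what the pooled change can be called. It is uncontrolled, its 'before' points differ by arm, and the preliminary comparison cannot detect drift that the arms share. This conclusion is structural and needs no assumed number.

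Its size cannot be fixed from the document. Untreated drift of about 0.06 to 0.35 SD is possible under the assumed correlations, with less in controls, so the bias of the pooled figure should lie below the experimental arm's drift. The power range for the check (18-38% at 0.25 SD, 55-91% at 0.5 SD) rests on 36 per arm, a two-sided 0.05 test and ρ of 0.5 to 0.8, of which only the 36 follows from the plan.

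The randomised comparison is unaffected. The change is worth making, but the primary analysis does not depend on it.

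**What to change.** In the Statistical analysis section:

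1. Delete the stated purpose of measuring an overall treatment effect, and delete the examine-then-pool step.
2. State that the effect of CBT is estimated only from the randomised comparison at the end of the waiting period.
3. Always report the change from before to after CBT by arm, and pooled if wanted, with 95% confidence intervals, labelled as descriptive within-patient change. Show the control arm's change during the wait beside it.

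The cost is wording only: no extra patients, visits or data. The downside is that one supportive analysis loses its inferential status.

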**Figure 1 F1:**
[figure not shown]
Flow chart study design.

The SCID-I will be administered by telephone, by psychologists who received a specific training for this.

All patients will then be asked to complete a set of questionnaires that assess the baseline primary and secondary outcomes via the web (see Table 1). If patients prefer paper and pencil completion, these questionnaires will be sent. After completion of the first baseline assessment, patients will be randomly assigned to the experimental or waiting-list control condition. Randomization will be stratified by gender, disease type and type of medical center (peripheral or academic) and will be performed by an independent employee at the Department of Clinical Epidemiology and Biostatistics of the AMC.

**Table 1 T1:** Overview assessment schedule

**Measure**	**Description**	**T**_**baseline**_	**T**_**follow-up after waiting/baseline before CBT**_	**T**_**mid-treatment**_	**T**_**follow-up after CBT**_
*Screening SCID*-*I*^*^	DSM-IV-TR				
	Axis I disorders				
*Primary Outcome*					
IBDQ^**^	Inflammatory Bowel Disease Questionnaire	E C	C	E C	E C
*Secondary Outcome*					
SF-36^**^	MOS 36-item Short-Form Health Survey	E C	C	E C	E C
HADS^**^	Hospital Anxiety and Depression Scale	E C	C	E C	E C
CES-D^**^	The Center for Epidemiologic Studies Depression Scale	E C	C	E C	E C
P-HBI^**^	Patient-based Harvey Bradshaw Index	E C	C	E C	E C
P-SCCAI^**^	Patient-based Simple Clinical Colitis Activity Index	E C	C	E C	E C
*Potential Mediators*					
DAS^**^	Dysfunctional Attitude Scale	E C	C	E C	E C
IPQ-R^**^	Illness Perception Questionnaire-Revised	E C	C	E C	E C
UCL^**^	Utrechtse Coping Lijst	E C	C	E C	E C

*Experimental Condition* (*E*) *and Waiting list Control Condition* (*C*).

^***^*Interview that is administered by telephone.*

^****^*Web-based questionnaire.*

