### Withdrawal

Subjects can withdraw from the study at any time for any reason if they wish to do so without any consequences. Nevertheless, we will ask those who withdraw from CBT treatment if they are willing to complete the web-based questionnaires at the respective time intervals.

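### The comparison labelled ITT uses ANOVA, ANCOVA and gain scores, which on observed data leave out randomised patients with no follow-up score

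*Protocol article*

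**What the plan says.** The Statistical analysis section of the protocol article names its methods. It opens with "Analyses of covariance will be conducted to determine the extent to which treated patients (experimental condition) show more improvement" than waiting-list controls. It then specifies a two-way factorial ANOVA with condition as the between-factor "and the within-factor assessments will be used", and returns to ANCOVA to bring in the stratification variables. Effect sizes are to be built from mean gain scores. For therapy effects, "data will be analysed on an intention to treat (ITT) as well as treatment completer basis". The second set is defined by treatment received: "The completers sample will include patients who attend at least 5 CBT sessions". The ITT set is not defined further, and the article does not say how missing outcomes are handled.

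Three other places bear on this:

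- **Sample size.** Missing data are expected: "Given a potential attrition rate of 10" per cent, 40 patients per arm are to be included so that at least 34 remain.
- **Withdrawal.** Answering after stopping treatment is voluntary: "we will ask those who withdraw from CBT treatment if they are willing to complete the web-based questionnaires". The request is worded for those who leave CBT. Waiting-list patients who leave before CBT are not mentioned.
- **Methods and design (text after Figure 1) and Table 1.** "After completion of the first baseline assessment, patients will be randomly assigned to the experimental or waiting-list control condition", so baseline is complete by design. Waiting-list patients wait 3.5 months and then "complete a follow-up after waiting/baseline before CBT assessment before starting treatment". Their mid-treatment and final assessments come later, during and after their own CBT.

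**The concern.** An ITT comparison should account for every randomised patient. The methods named for it need an observed outcome, and the plan expects some outcomes to be missing. Run as written on the data that arrive, the analysis carrying the ITT label would be a comparison of patients with follow-up data.

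What is at stake is mainly bias. Patients who stop CBT and also stop answering are plausibly those who benefited least. If they leave the CBT arm's mean, the estimate is too favourable and moves closer to the completer result that it is meant to stand apart from. Some precision is also lost in a small trial.

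**Working it through.** **1. The plan's own allowance.** Inputs from Sample size: 34 per arm needed, 10% attrition, 40 per arm recruited.

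- Required: 34 / 0.90 = 37.8, so 38 per arm. The plan takes 40.
- Remaining: 40 × 0.90 = 36 per arm, which is above 34. Attrition could reach 1 − 34/40 = 15% before 34 is breached.

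The allowance therefore covers the loss in numbers. It does nothing about which patients are lost. (The 34 itself does not reproduce as an ordinary two-sided two-group comparison at 0.5 SD, which needs 64 per arm by t-test. That is a separate matter and nothing below depends on it.)

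**2. What each named method needs from a patient.**

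- Factorial repeated-measures ANOVA: a value at every level of the within-factor.
- ANCOVA: an observed outcome.
- Gain score, and Cohen's *d* built on it: a value before and a value after.

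None of the three keeps a randomised patient without a follow-up score unless something is imputed first.

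**3. Who is lost in the randomised phase.** The experimental arm has baseline, mid-treatment and follow-up after CBT. The waiting-list arm has baseline and follow-up after waiting. Methods and design describes the 3.5-month wait as matching the experimental arm's treatment and follow-up period, so both arms share two time points.

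- No follow-up score: lost under all three methods.
- Only mid-treatment missing: not lost if the contrast is limited to the two shared time points, and not lost from ANCOVA.
- Stopped CBT but kept answering: not lost.

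**4. How many.** At 10% attrition, 80 × 0.10 = 8 patients lack the outcome and 72 remain, 36 per arm.

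If the ANOVA also required mid-treatment in the experimental arm, with 10% missing independently at each assessment (an assumption, not in the article), that arm would keep 40 × 0.9 × 0.9 = 32.4 and the control arm 36, about 68 of 80.

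**5. Illustrative bias.** Assumptions: CBT-arm dropouts gain nothing relative to control, the remaining CBT patients gain 0.50 SD, and control dropouts resemble other controls.

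- 10% lost: 0.90 × 0.50 + 0.10 × 0 = 0.45 SD. Complete cases show 0.50, and 0.50/0.45 = 1.11, an 11% overstatement. With the article's SD of 59, 0.05 × 59 is about 3 IBDQ points.
- 15% lost: 0.85 × 0.50 = 0.425 SD, and 0.50/0.425 = 1.18, an 18% overstatement.

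A simulation under different assumptions (true effect 0.50 SD, baseline to follow-up correlation 0.68, CBT-arm dropouts drawn from the half with the poorer change, control dropouts at random) gave a complete-case change-score estimate of 0.57 SD with 10% missing and 0.66 SD with 20% missing.

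**6. Does a mixed model alone remove this?** No. In the example in step 5, a dropout with no value after baseline adds almost nothing about the treatment effect. A likelihood-based model under missing at random would still return about 0.50, and so would standard multiple imputation. These methods gain where a dropout has a mid-treatment value, or where baseline predicts who drops out.

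**The case against.** The strongest reply is that the article says nothing about deleting incomplete patients. ANOVA or ANCOVA on imputed data keeps everyone and is compatible with ITT. A journal article commonly leaves the imputation rule to the full protocol or SAP, which are not shown. In addition, patients who leave CBT are asked to keep answering, which is how ITT data are obtained.

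Much of this stands. The loss of patients is conditional, not fixed by the text, and the absence of an imputation rule is not itself the point. The point is that the article names the methods, attaches the ITT label and expects attrition, and no wording reconciles the three.

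Several stronger readings are tempting, but the article does not support them:

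- *Every patient with any missing assessment is dropped.* Baseline is complete before randomisation, and a missing mid-treatment score alone need not exclude anyone.
- *No balanced within-factor exists.* Both arms have baseline and an assessment at roughly 3.5 months. What is missing is a statement that the contrast is limited to these two.
- *Only about 65 of 80 remain.* That figure (80 × 0.9 × 0.9) requires two assessments after baseline in both arms, whereas controls have one in the randomised phase. It also treats a single overall attrition rate as independent loss at each visit.
- *The ITT analysis collapses into the completer analysis.* Completers are defined by sessions attended, so patients who stop CBT but answer still separate the two.

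**Conclusion.** The point holds in a limited form. Followed as written on observed data, the named methods do not deliver the ITT set: about 8 of 80 randomised patients would be left out at the plan's own attrition rate. The 72 of 80 rests only on the article's figures.

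The size of any bias rests on assumptions about the dropouts. If those in the CBT arm gained nothing, it is 0.05 SD at 10% loss. It could be larger if loss is heavier or more selective, and smaller or absent if control dropouts are similarly selected or if most patients who stop CBT keep answering. If a full protocol or SAP already specifies imputation of all randomised patients, what remains is to make the article's wording agree with it. The matter is worth settling before analysis, but it does not threaten the design.

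**What to change.** For the randomised ITT contrast:

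1. Replace the factorial ANOVA with a likelihood-based linear mixed model, or use ANCOVA after multiple imputation, in all randomised patients.
2. State the assessments that enter: baseline, the experimental arm's mid-treatment value, and the matched assessment at roughly 3.5 months (follow-up after CBT versus follow-up after waiting). The treatment effect is the contrast at the matched assessment. In the mixed model, treat baseline as one of the repeated measurements, because patients with baseline only would drop out if it were just a covariate.
3. Adjust for gender, disease type and type of center.
4. State that waiting-list patients who leave before CBT stay in this contrast.
5. Add one sensitivity analysis in which CBT-arm dropouts do no better than controls. This is essential, because the main methods assume data missing at random.

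The cost is a change of wording and modest extra programming, with no further patients or data. The sensitivity estimate may be less favourable than the main one.
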